### Safety

Any adverse events or discomfort throughout the course of the trial will be recorded by patients and data collectors. Participants may withdraw from the study for any reason at any time. The researchers will record the reasons on case report forms.

### Statistical analysis

Data are analysed using SPSS V.21.0 (Chicago, IL, USA), with the significance level set at 0.05 (two-tailed) by statisticians who are independent of the research team. Patient baseline characteristics are summarised by treatment arm by employing appropriate summary statistics to assess baseline comparability only. Data analysis is conducted with the intention-to-treat (ITT) principle and a per-protocol (PP) analysis. To ensure the comparability of baseline conditions between the two groups and allow the presence of noncompliant patients, the ITT population consists of all randomised participants. In addition, at least one follow-up will be recorded after the intervention. According to the patients’ actual lifestyle adjustment after random grouping, the PP analysis studies the patients who completed the trial and did not violate the protocol. This process is an explanatory, supplementary analysis, contributing to study objectivity. We calculate the effective rates at 1 and 3 months for the primary outcome and compare the intervention and control groups by using the χ^2^ test. For secondary outcomes, continuous variables, including THI, visual analogue scale and WRS, are compared between the two groups at all follow-up time points by using a *t* test or the Wilcoxon signed-rank test as appropriate. Categorical variables, such as different degrees of hearing loss, are compared using the χ^2^ test or Fisher’s exact test. For dropout analysis, we use multiple imputations for ITT analysis. A sensitivity analysis is performed to assess the effect of missing data assumptions.

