#### Exclusion criteria

The exclusion criteria are as follows:
Previous disease or surgery in the affected earHearing loss from an identified aetiology, including head trauma, conductive hearing loss, Meniere’s disease or tumourInability to complete relevant assessments, such as cognitive impairment and mental disorder assessmentsSerious comorbid conditions, such as progressive central disorder or life-threatening conditionsAny reason, in the investigator’s opinion, that prohibits inclusion.

The criteria for trial termination and dropout are as follows: the patient develops a severe disease unrelated to participation in the trial; the patient chooses other treatments and drugs; the patient requests termination or withdraws; the patient no longer receives the trial treatment regimen and examination.

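### The plan does not fix one ITT population, and its dropout criteria do not separate stopping the regimen or switching treatment from ending assessment

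*Protocol article*

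**What the plan says.** All references are to the protocol article.

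- **Statistical analysis, population.** The ITT set is introduced with a purpose, "To ensure the comparability of baseline conditions between the two groups and allow the presence of noncompliant patients", and then defined in two adjacent sentences: "the ITT population consists of all randomised participants. In addition, at least one follow-up will be recorded after the intervention". The per-protocol analysis of completers follows and is described as supplementary.
- **Statistical analysis, missing data.** "For dropout analysis, we use multiple imputations for ITT analysis". Then: "A sensitivity analysis is performed to assess the effect of missing data assumptions".
- **Exclusion criteria, closing paragraph on termination and dropout.** The list includes "the patient chooses other treatments and drugs" and "the patient no longer receives the trial treatment regimen and examination".
- **Outcome measure evaluation.** After baseline there are two assessments, at 1 and 3 months.
- **Sample size.** Assumed rates are 50% (intervention) and 10% (control), with 23 per group raised to 28 for a 20% loss, or 56 in total.

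**The concern.** There are two linked problems.

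First, the two population sentences can give two different denominators. One analyst would include everyone randomised and impute. Another would require at least one recorded follow-up and leave out anyone never seen after baseline. The second set is usually called modified ITT, and membership in it depends on an event after randomisation.

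Second, the dropout list puts a change of treatment next to the end of regimen and examination. It does not say that a patient who switches is still tested at 1 and 3 months. If testing stops, that outcome is missing by design.

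The article itself suggests that such loss may depend on the outcome. The Discussion says that patients who do not improve tend to give up hope and stop therapy, and the Blinding section says that patients know their treatment. With 28 patients per arm, a few exclusions can move the primary comparison.

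**Working it through.** **1. The plan's own figure.** Inputs from Sample size: U-values 1.65 and 1.28, P1 = 0.5, P0 = 0.1, so P = 0.3.

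n = (1.65 + 1.28)² × 2 × 0.3 × 0.7 / (0.5 − 0.1)² = 8.5849 × 0.42 / 0.16 = 22.54, rounded up to 23 per group.

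23 × 1.2 = 27.6, rounded up to 28 per group, 56 in total. The stated figures reproduce. The allowance is 56 − 46 = 10 patients. An all-randomised ITT set does not change the 56.

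**2. Who is in the set under each reading.**

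| Patient | Follow-up sentence is not a condition | Follow-up sentence is a condition |
|---|---|---|
| Seen at 1 and 3 months | in, observed | in, observed |
| Seen at one visit only | in, other visit imputed | in, other visit imputed |
| Seen at neither visit | in, both visits imputed | out, not imputed |

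The readings differ only in the last row. The allowance of about 10 of 56 is therefore a ceiling on planned exclusions, because some patients lost to follow-up will have had a 1-month visit.

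**3. Worst case for equal loss.** Assumption, not in the documents: a share d of each arm is lost, all of them non-responders, and all are excluded. Each rate p then reads p/(1 − d).

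| d | Intervention (50%) | Control (10%) | Difference (40 points) |
|---|---|---|---|
| 10% | 55.6% | 11.1% | 44.4 |
| 20% (planned) | 62.5% | 12.5% | 50.0 |
| 30% | 71.4% | 14.3% | 57.1 |

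If loss is unrelated to outcome, the expected rates stay at 50% and 10%. At the planned 20%, equal in both arms, loss ranging from unrelated to outcome up to all non-responders gives an apparent difference between 40 and 50 points.

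**4. Direction when loss is unequal.** Assumed counts, χ² test without continuity correction:

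- All randomised: 8/28 (28.6%) versus 3/28 (10.7%), p = 0.093.
- Six intervention non-responders excluded: 8/22 (36.4%) versus 3/28, p = 0.030.
- Six control non-responders excluded: 8/28 versus 3/22 (13.6%), p = 0.21.

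The same number of exclusions moves the result either way, depending on the arm.

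**The case against.** The strongest reply is that the follow-up sentence does not expressly set a condition. It says a follow-up will be recorded, which may only describe data collection. The stated aim of keeping noncompliant patients and the imputation of dropouts both fit the inclusive reading. This stands as far as it goes: the text is ambiguous and is not an express exclusion. It does not settle which set will be analysed, and an entry condition remains a natural reading.

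A reader might infer more, namely that non-responders leave the primary analysis and that the effective rate is inflated by 1/0.8 = 1.25, in favour of the intervention. The documents do not support that, for four reasons.

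- The dropout list does not say that these patients are removed from the analysis. At most, patients with no visit leave the ITT set. The others are imputed, and a sensitivity analysis is planned.
- An entry condition does not by itself contradict imputation, since a patient seen only once is in the set and can be imputed for the other visit.
- How well imputation works depends on a model the article does not show and may fairly leave to an analysis plan. With 1-month thresholds in the model, early non-recovery would inform the 3-month value. A patient with no visit has only baseline data to offer.
- The direction is unknown. The lifestyle programme asks more of patients, but it also brings more telephone contact. Unblinded controls receive only routine care and might leave more often, although they are offered the programme at the end. Free assessments and other retention measures apply to all participants.

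**Conclusion.** The point holds in limited form. The article does not fix one ITT set, and its dropout criteria leave open whether patients who switch treatment are still assessed. Both are faults in the text as it stands, because following it could exclude patients, or leave them unobserved, for reasons related to non-recovery.

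The documents do not determine the size of any bias. The figure of 62.5% versus 12.5% is a worst case that needs 20% loss in each arm, every lost patient a non-responder, and every one excluded. It is not an expected result, and it does not bound unequal loss. No claim about which arm would be favoured is justified.

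**What to change.** 1. In Statistical analysis, define the ITT population as all 56 randomised patients in their allocated group, and delete the follow-up sentence as a condition. If that set is still wanted, call it modified ITT and make it secondary.
2. State that patients who meet the termination and dropout criteria stay in the ITT set. Separate stopping the regimen or taking other treatment from leaving follow-up, and keep the scheduled 1- and 3-month audiograms unless consent is withdrawn.
3. Analyse observed results where they exist, and use the planned multiple imputation where they do not.
4. Counting missing outcomes as not effective is one reasonable choice for the sensitivity analysis already planned, but not the only one.

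The cost is a wording change, slightly more follow-up effort for audiograms that are already scheduled, and possibly a smaller estimated effect. The Trial status section says both that recruitment is under way and that it was completed in October 2019. If follow-up has closed, missed visits cannot be recovered. The population definition and the handling of dropouts can still be fixed before any unblinded analysis.

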**Methods:**

This study is a clinical randomised trial that involves 56 patients diagnosed with ISSNHL but who have had incomplete recovery after initial management (at least 2 weeks of routine Western medical treatment). The study is performed in accordance with the sudden hearing loss clinical guideline of the American Academy of Otolaryngology–Head and Neck Surgery, published in 2012. Participants are randomly distributed into two groups: the healthy lifestyle modification group based on TCM and the control group (1:1 ratio). Patient follow-up lasts for 3 months. The primary outcome measure is the effective rate of hearing improvement, which is defined as the proportion of patients with at least 15 dB of improvement in the average thresholds of hearing loss frequency. The secondary outcome measures are improvements in word recognition score, Tinnitus Handicap Inventory and visual analogue scale for ear blockage and dizziness. Assessments are made at baseline and after lifestyle modification for 1 and 3 months.

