### Outcome measure evaluation

The outcomes are evaluated at baseline and at 1 month and 3 months after the participant starts the intervention.

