### Primary outcome measure

The primary outcome measure will be the effectiveness of hearing improvement. This will be taken as the percentage of patients with an improvement of at least 15 dB in their impaired frequency compared with the baseline. On the basis of the American Academy of Otolaryngology–Head and Neck Surgery 2012 practice guideline on ISSNHL, an improvement within 10 dB HL of initial HL or within 10 dB HL of the unaffected ear’s hearing threshold is defined as complete recovery. An improvement of more than 30 dB HL in pure tone average (PTA) from pretreatment hearing levels is defined as significant recovery; an improvement of 15–30 dB HL is defined as effective recovery. An improvement of less than 15 dB HL in PTA is defined as no recovery [1, 20].

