### Sample size

To the best of our knowledge, no randomised pilot study has been conducted to assess the effectiveness of lifestyle changes on ISSNHL. Therefore, we are not able to calculate the sample size based on previous studies. On the basis of our retrospective analysis (unpublished) and clinical experience, the efficiency ratio of the intervention group is conservatively estimated to be 50%, and the natural recovery rate over 2 weeks is 10% [9]. Using a formula [23] to calculate the sample size of optimal treatment in the clinical trial and considering α = 0.05, β = 0.1, by the table of normal distribution quantifiers *U*_α(0.05)_ = 1.65, *U*_β(0.1)_ = 1.28, we require a patient sample size of 23 per group. We allow for a 20% loss to follow-up (approximately 10 cases), with a total sample size of 56 patients (28 per group) in the study.
$$ {\displaystyle \begin{array}{l}n={\left( U\alpha + U\beta \right)}^22P\left(1-P\right)/\left({P}_1-{P}_0\right)2,\\ {}P=\left({\mathrm{P}}_1+{\mathrm{P}}_0\right)/2\times 100\%,\end{array}} $$

*P*_0_: original efficacy, *P*_1_: expected efficacy.

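### The primary effective rate is compared at both 1 and 3 months under one 0.05 level, and the protocol does not say which visit, or which combination, decides the trial.

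*Protocol article*

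**What the plan says.** Four sections of the protocol article bear on the point.

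- **Primary outcome measure** defines the outcome as the "percentage of patients with an improvement of at least 15 dB in their impaired frequency compared with the baseline". No visit is attached. The abstract's definition has none either.
- **Outcome measure evaluation** puts the two follow-up visits on equal terms: "The outcomes are evaluated at baseline and at 1 month and 3 months after the participant starts the intervention".
- **Statistical analysis** assigns both visits to the primary outcome: "We calculate the effective rates at 1 and 3 months for the primary outcome and compare the intervention and control groups". The test is χ². The level is given once, for all analyses: "with the significance level set at 0.05 (two-tailed".
- **Sample size** plans one comparison of two proportions, "considering α = 0.05, β = 0.1". Its control rate of 10% is described as natural recovery over 2 weeks, which corresponds to neither visit.

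The abstract adds "Patient follow-up lasts for 3 months". That fixes when observation ends but does not make the last visit primary.

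**The concern.** A confirmatory trial needs one rule, fixed in advance, that turns the primary data into a yes or a no. Here the primary outcome yields two p-values and the article gives no way to combine them or choose between them. Two things follow.

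First, if the investigators were to claim efficacy on whichever visit is significant, the chance of a false claim would exceed the stated 5%.

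Second, the visits may disagree. The daily lifestyle form is required for 1 month only, while follow-up runs to 3 months, so an early difference that fades and a late one that emerges are both conceivable. The abstract says that positive results could support recommending the programme as salvage therapy, but the reader cannot tell which pattern of results would be positive.

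**Working it through.** **Inputs from the protocol article:** two tests of the primary outcome (1 and 3 months); level 0.05 two-tailed; P1 = 50%, P0 = 10%; normal quantiles 1.65 and 1.28; 23 per group, 56 in total after allowing for 20% loss.

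**Input not in the documents:** the correlation r between the two visits' test statistics. It is assumed and shown as a range.

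**Step 1: reproduce the plan's sample size.** P = (0.50 + 0.10)/2 = 0.30.

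n = (1.65 + 1.28)² × 2 × 0.30 × 0.70 / (0.50 − 0.10)² = 8.5849 × 0.42 / 0.16 = 22.5, rounded up to 23 per group.

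Total: 46 × 1.2 = 55.2, taken up to 56. The figure reproduces as a calculation for a single comparison. It does not show which visit that comparison is.

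**Step 2: type I error under each possible success rule.** Under no treatment effect:

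- Either visit suffices: error = 1 − P(|Z1| < 1.96, |Z2| < 1.96), with Z1 and Z2 bivariate normal and correlation r. For r = 0 this is 1 − 0.95² = 0.0975.
- Both visits required: error = 0.05 + 0.05 − (either-visit error).
- One named visit: error = 0.05.

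| Assumed r | Either suffices | Both required | One named visit |
|---|---|---|---|
| 0 | 0.0975 | 0.0025 | 0.05 |
| 0.5 | 0.0907 | 0.0093 | 0.05 |
| 0.7 | 0.0835 | 0.0165 | 0.05 |
| 0.8 | 0.0781 | 0.0219 | 0.05 |
| 0.9 | 0.0704 | 0.0296 | 0.05 |
| 0.95 | 0.0646 | 0.0354 | 0.05 |

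As r approaches 1 the first two columns both approach 0.05.

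**Step 3: check with the actual test at the planned size.** χ² tests were simulated at 23 and 28 per group, with a common response rate of 10% or 30% at both visits and within-patient correlation of 0, 0.5 or 0.8. The either-visit error ran from 0.069 to 0.105. A single test ran from 0.044 to 0.054. The normal approximation in step 2 is therefore adequate here.

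**Step 4: cost of keeping both visits with an equal split of alpha.** At two-sided 0.025 per visit, the plan's formula gives (2.241 + 1.282)² × 0.42 / 0.16 = 32.6, so 33 per group before loss to follow-up. With the plan's 20% allowance that is 66 × 1.2 = 79.2, or 80 in equal groups, against 56.

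**The case against.** The strongest reply is that the article says less than a critic might read into it.

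- **No success rule is stated.** A reader might infer that significance at either visit would be enough and that the 5% level is therefore breached. The text does not say so. If both visits were required, the error would be below 5%. If one visit were only supportive, there would be no inflation. This part stands: the inflation is conditional.
- **No adjustment is mentioned, but none is ruled out.** That each visit is tested at the full 0.05 is an inference from the single general level. An analysis plan that is not shown could split alpha or order the tests. This also stands, so a missing adjustment is not the point made here.
- **The correlation may be high.** Both tests use the same patients, the same baseline and the same 15 dB threshold, in a population that the article expects to recover little after the first 14 days. Independence is unrealistic, so 9.75% is an upper reference rather than an estimate, and values near 7% or lower are plausible.
- **Three months is not the only defensible choice.** The daily form runs for 1 month, so a case could be made for that visit.

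These replies do not settle which visit decides. The time point is part of the definition of the primary outcome and belongs in the protocol. The protocol does not merely leave it open: it assigns both comparisons to the primary outcome.

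**Conclusion.** The point holds as an undefined success criterion. The protocol article attaches two comparisons to its primary outcome and designates no primary visit, no both-required rule and no testing order. That finding rests on the text alone.

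The size of the possible error inflation rests on two assumptions: that either visit would count as success, and a value for the between-visit correlation. Under the first, the two-sided type I error is about 7% to 9% for correlations of 0.9 to 0.5. The documents do not support the flat statement that the trial's type I error exceeds 5%, nor the statement that it is doubled. What they support is that the error cannot be determined from the plan: it is below 5% if both visits are required, 5% if one is named, and above 5% if either suffices.

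**What to change.** State in the protocol, and carry into any analysis plan, that the primary analysis is the between-group comparison of the effective rate at 3 months, at two-sided 0.05. Three months is the end of the stated follow-up. Make the 1-month rate a secondary outcome, or test it only if the 3-month comparison is significant.

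Date and document the choice before anyone sees unblinded results. The Trial status section says both that recruitment is ongoing and that it was completed in October 2019, so this timing matters: a choice made after the results are known would be the selective choice that it is meant to prevent.

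Cost: one sentence of text, and the loss of any primary claim based on 1 month alone. Naming one visit does not change the sample size, because the plan already sizes a single comparison. (That calculation uses the one-sided quantile 1.65 beside a two-tailed analysis, which is a separate matter that this fix neither causes nor cures.) Keeping both visits with a split alpha would instead need 33 per group before loss to follow-up, against the planned 23.

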## Background

Idiopathic sudden sensorineural hearing loss (ISSNHL) is a common otologic emergency that presents mostly as an acute hearing loss with an abrupt occurrence. ISSNHL is a hearing loss of more than 30 dB that occurs in at least three consecutive frequencies within 72 h [1]. Aside from hearing impairment, ISSNHL can be associated with dizziness, tinnitus and/or ear fullness/blockage. The ISSNHL incidence is approximately 5–30/100,000/year in developed countries, such as the USA, Sweden and Japan, as revealed by national surveys [1–4]. Detailed investigations suggested that only approximately 10% of patients with ISSNHL show a specific cause [5]. Several pathophysiological mechanisms, including microcirculation, autoimmune pathology, viral infection, intracochlear membrane rupture or haematologic problems, have been proposed despite the unidentified precise cause of ISSNHL [6]. ISSNHL may not be due to a single pathological change but to a spectrum of pathologies affecting the cochlea [7].

The most common treatment option for ISSNHL is administration of corticosteroids within the first 2 weeks [4]. A total of 49–89% of patients with ISSNHL will show recovery via systemic steroid therapy, whereas therapy displays no effects on other patients [8]. Spontaneous recovery occurs in 32–65% of the cases, usually within the first 14 days [9, 10]. However, recovery amongst patients who do not show improvement after 2 weeks is low [11]. Intratympanic steroid perfusion described in the US guidelines has been recommended as salvage therapy [1]. However, its clinical evidence remains controversial, and no existing consensus suggests the efficacy of intratympanic steroid therapy for ISSNHL [1, 12, 13]. Therefore, the failure of a 2-week treatment amongst patients with ISSNHL should be further studied, and alternate therapies should be developed.

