### Randomisation

When patients want to participate in the trial and meet the requirements, a research assistant who reviews and explains the study collects the patient’s basic demographic information and previous clinical data. Eligibility of the patient is ascertained, followed by provision of the written consent form. Before randomisation, the patients must have reassessed their hearing status with an otoscopic examination, hearing threshold tests (air conduction hearing thresholds measured at 250–8000 Hz, bone conduction hearing thresholds measured at 500–4000 Hz), word recognition scores (WRSs) and ear-specific immittance measurements (including tympanometry, static immittance and acoustic reflex measures). These measures can assess the patient’s baseline hearing state and exclude conductive hearing loss. According to the classification standard of hearing loss degree published by the World Health Organization in 1997, the average values of hearing thresholds of 500, 1000, 2000 and 4000 Hz were calculated and then divided into categories of mild (26–40 dB hearing loss [HL]), moderate (41–60 dB HL), severe (61–80 dB HL) and profound (≥ 81 dB HL). Patients were stratified by gender, age and degree of hearing loss. Patients of the same gender, with age differences within 3 years and with the same degree of hearing loss were classified in the same stratification.

A statistician who is not part of the clinical intervention uses the Statistical Package for the Social Sciences (SPSS) 21.0 (IBM, Chicago, IL, USA) to generate a randomisation code. This code is embedded into serially numbered, opaque envelopes. After a participant completes the baseline measures, and when the same stratification reaches two or an even number of patients, another research assistant opens the next envelope in the series to determine the participant group allocation. Patients in the same stratification are randomised for the two treatments with a 1:1 ratio.

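### Randomisation is 1:1 within matched strata, but the primary test is an unstratified chi-square, which is conservative if the strata are prognostic

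*Protocol article*

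**What the plan says.** **Design (protocol article, Randomisation).** The section states: "Patients were stratified by gender, age and degree of hearing loss". A stratum is narrow: "Patients of the same gender, with age differences within 3 years and with the same degree of hearing loss were classified in the same stratification". Allocation waits until a stratum can be split: "when the same stratification reaches two or an even number of patients, another research assistant opens the next envelope in the series". Balance is then required inside the stratum: "Patients in the same stratification are randomised for the two treatments with a 1:1 ratio". Read together, these sentences describe matched pairs, or small even-sized matched blocks.

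**Outcome (Primary outcome measure).** The outcome is binary, the "percentage of patients with an improvement of at least 15 dB in their impaired frequency compared with the baseline".

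**Analysis (Statistical analysis).** Effective rates at 1 and 3 months are calculated "for the primary outcome and compare the intervention and control groups by using the" χ² test, at a two-tailed 0.05. Baseline data are summarised only to judge comparability. The section names no stratified, matched or covariate-adjusted form of the primary comparison. The formula in the Sample size section also treats the arms as two independent groups.

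**The concern.** Matching on sex, age and severity makes the two arms more alike than two independent samples would be. If those factors predict recovery, outcomes within a stratum are positively correlated, and the difference between arms varies less from trial to trial than the independent-samples formula assumes. The ordinary chi-square test uses the larger, independent-samples variance. The gain in precision that the design went to some trouble to obtain is then not used: the test rejects less often than its nominal level, and an interval built on the same variance would be too wide.

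The stake is modest but real in a trial of 56 patients. The expected 50% response rests on an unpublished retrospective analysis and clinical experience. If the true effect is smaller than planned, the lost precision could decide whether it is detected.

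**Working it through.** **Inputs from the protocol article.** P1 = 50%, P0 = 10%, 28 per group, 23 per group before allowance for loss, U values 1.65 and 1.28 (Sample size); two-tailed 0.05 and χ² test (Statistical analysis); 1:1 within matched strata (Randomisation).

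**Assumptions.** The within-pair outcome correlation φ is not given, so it is varied over 0, 0.1, 0.2 and 0.3. All 56 patients are taken to form 28 complete pairs.

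**1. The plan's own figure.** P = (0.50 + 0.10)/2 = 0.30.
n = (1.65 + 1.28)² × 2 × 0.30 × 0.70 / 0.40² = 8.585 × 0.42 / 0.16 = 22.5, rounded up to 23 per group. Then 46 + 10 = 56. The figure reproduces, with an independent-groups formula that contains no term for matching.

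**2. Standard error at 50% versus 10%.**
Unpaired variance: (0.25 + 0.09)/28 = 0.34/28, so SE = 0.110.
Matched variance: [0.25 + 0.09 − 2φ√(0.25 × 0.09)]/28 = (0.34 − 0.30φ)/28.

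| φ | True SE | Unpaired SE ÷ true SE | 95% half-width, unpaired | 95% half-width, true |
|---|---|---|---|---|
| 0 | 0.110 | 1.00 | 0.216 | 0.216 |
| 0.1 | 0.105 | √(0.34/0.31) = 1.05 | 0.216 | 0.206 |
| 0.2 | 0.100 | √(0.34/0.28) = 1.10 | 0.216 | 0.196 |
| 0.3 | 0.094 | √(0.34/0.25) = 1.17 | 0.216 | 0.185 |

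The range cannot go much higher. With response rates of 50% and 10%, the largest possible φ is (0.10 − 0.50 × 0.10)/√(0.25 × 0.09) = 0.05/0.15 = 0.33.

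**3. Size and power.** These come from simulation of 28 pairs, 400,000 trials per case, two-sided 5%. Pearson chi-square is set against McNemar without continuity correction.

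| φ | Chi-square size, both arms 30% | Chi-square size, both arms 10% | Power at 50% vs 10%: chi-square / McNemar | Power at 35% vs 10% (assumed): chi-square / McNemar |
|---|---|---|---|---|
| 0 | 5.2% | 5.3% | 93.6% / 91.8% | 62% / 59% |
| 0.1 | 4.1% | 4.1% | 94.7% / 94.5% | 63% / 64% |
| 0.2 | 3.0% | 3.1% | 95.7% / 97.0% | 64% / 70% |
| 0.3 | 2.0% | 2.1% | 96.8% / 99.3% | 65% / 77% |

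McNemar's own size with both arms at 30% stays near 4.3% throughout. At the planned effect, chi-square power rises slightly with φ, because the observed difference becomes less variable while the rejection threshold is unchanged.

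**The case against.** The strongest reply is that the unstratified test remains valid: its error is on the safe side, its size depends on a correlation that nobody has stated, and at φ = 0 there is no error at all. At the planned effect with all 28 pairs, power is above the 90% target whichever test is used. All of this stands, and it limits the point to efficiency. It does not remove the mismatch, because the article itself names the primary test and that test does not use the randomisation groups. Supporting analyses may well be set out in a statistical analysis plan that is not shown; their absence from the article is not criticised here.

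A reader might infer more than the document supports, in four ways.

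- **That false positives are inflated.** The direction is the opposite: the size falls below 5%.
- **That this mismatch leaves the trial underpowered at its planned effect.** It does not: chi-square power is about 94% to 97% with 28 pairs. With only 23 evaluable per group, chi-square power for independent groups is about 88%, but that comes from attrition and from the 1.65 quantile in the sample size formula, not from ignoring the strata.
- **That the plan errs by not adjusting for time since onset.** The Background says that "recovery amongst patients who do not show improvement after 2 weeks is low". That contrasts recovery before and after day 14, and every enrolled patient is past day 14. The article gives no recovery gradient between 14 days and 1 year. Chance imbalance in this factor is covered by randomisation and the error rate of the test.
- **That a fully adjusted logistic model is the obvious remedy.** About 28 × 0.50 + 28 × 0.10 = 16.8 responders are expected, with about 3 in the control arm. Five slopes on that number of events would be fragile.

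**Conclusion.** The point holds as a mismatch between design and analysis, with a conservative and probably modest effect. For an assumed φ of 0.1 to 0.3, the nominal 5% test has a true size of about 4% down to 2%, and the standard error at 50% versus 10% is 5% to 17% too large. At the planned effect there is no worrying loss of power. At an assumed 35% versus 10%, the chi-square gives up about 1, 6 and 12 percentage points to a paired test at φ = 0.1, 0.2 and 0.3.

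These sizes rest on the assumed correlations and on 28 complete pairs. The direction rests only on the strata being positively prognostic. A positive result under the planned chi-square would not be undermined by this point; a borderline negative one would be harder to interpret.

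**What to change.** 1. Record the stratum and pair identifier in the data set when the envelope is opened. Age within 3 years does not define fixed bands, so the groups may not be recoverable afterwards from age, sex and hearing-loss degree alone.
2. Make the 3-month comparison of effective rates respect the randomisation, and treat the 1-month comparison in the same way. Use a Cochran-Mantel-Haenszel test and a risk difference stratified by randomisation stratum, with a 95% confidence interval. This form also copes with strata of more than two patients, which the Randomisation section allows. The alternative is a parsimonious model adjusted for sex, age and hearing-loss degree, with a penalised fit if responders are few.
3. Keep the unadjusted chi-square as a sensitivity analysis. Adjustment for time since onset can be an optional further one.
4. Fix the choice before unblinded data are seen.

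The cost is a few lines of wording and minor programming; the stratification factors are already collected. There is a small statistical price: if the strata turn out not to be prognostic, a pair-level test is slightly less powerful (about 92% against 94% at 50% versus 10%). Pairs with a missing member also contribute nothing to a complete-case pair-level test, so the analysis should be run within the multiple imputation already planned.
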